#### Compensation for injury

Ingevolge artikel 7 van de Wet op medisch wetenschappelijk onderzoek met mensen (Stlb. 1998, 161) is voor de deelnemende proefpersonen een verzekering afgesloten die de door het onderzoek veroorzaakte schade door dood of letsel van de deelnemende proefpersonen dekt. Deze verzekering voldoet aan de bepalingen van het Besluit Verplichte verzekering bij medisch-wetenschappelijk onderzoek met mensen (Stlb. 2003, 266).

Aan het onderzoek deelnemende proefpersonen zullen schriftelijk worden ingelicht over deze verzekering.

Elke aan het onderzoek participerende instelling draagt zorg voor de verzekering van de in de eigen instelling te includeren proefpersonen.

Elk deelnemend centrum heeft ook een aansprakelijkheidsverzekering als bedoeld in art. 7 WMO.

## **10. ADMINISTRATIVE ASPECTS AND PUBLICATION**

### **10.1 Handling and storage of data and documents**

Data will be handled confidentially and anonymously. To be able to trace data to an individual subject, a subject identification code list will be used. Participating subjects will be registered by a 5-digit number that will be used to link the data to the subject. This personal code will be on all forms retrieved from participants. The key to the code is safeguarded by the investigator. The handling of personal data will comply with the Dutch Personal Data Protection Act (in Dutch: De Wet Bescherming Persoonsgegevens, Wbp).

Serum and cordblood will be stored for 5 years at minus 80 degrees anonymously and coded as mentioned above.

## **10.2 Amendments**

Amendments are changes made to the research after a favourable opinion by the accredited METC has been given. All amendments will be notified to the METC that gave a favourable opinion.

## **10.3 Annual progress report**

The sponsor/investigator will submit a summary of the progress of the trial to the accredited METC once a year. Information will be provided on the date of inclusion of the first subject, numbers of subjects included and numbers of subjects that have completed the trial, serious adverse events/ serious adverse reactions, other problems, and amendments.

## **10.4 End of study report**

The investigator will notify the accredited METC of the end of the study within a period of 8 weeks. The end of the study is defined as the last patient's last visit.

In case the study is ended prematurely, the investigator will notify the accredited METC, including the reasons for the premature termination.

Within one year after the end of the study, the investigator/sponsor will submit a final study report with the results of the study, including any publications/abstracts of the study, to the accredited METC.

| Hoeger
2004 (6)            | 11 lifestyle
only               | 500-1000
kcal/day
deficit                          | 24                      | >25              | OR 8,97
at > 3%
weight
loss | 2         |                                                              |
| Tang
2006(7)               | 74
6 drop-
outs              | Dietary advice
with
500 kcal
reduction/day      | 24                      | >30              |                                      | 4         | 58%
improvement in
menses                              |
| Palomba
2007(8)            | 20                                 | 800 kcal
deficit/day                                  | 24                      | 30 - 35          | 5                                    | 2         |                                                              |

| Anovulatory(ov-) and ovulatory patients(ov+) |                         |                          |                         |                  |                |                                                           |                              |
|----------------------------------------------|-------------------------|--------------------------|-------------------------|------------------|----------------|-----------------------------------------------------------|------------------------------|
| article                                      | subjects                | intervention
Kcal/day | duration
in
weeks | inclusion
BMI | ovulation      | pregnancy                                                 | resumption
regular cycles |
| Clark
1998(9)                             | 87
20 drop-
outs  | lifestyle
program     | 24                      | >35              | 60 of 67       | -18
spontaneous
-34 after
fertility
treatment |                              |
| Crosignani
2003 (10)                      | 33 -
27 ov-
6 ov+ | 1200
kcal/day         | 28                      | >25              | 15 of
27ov- | 10                                                        | 18 of 27ov-                  |
| Moran
2003(11)                            | 45
14 drop-
outs  | 1500
kcal/day         | 12                      | >35              |                | 3                                                         | 11 of 25 ov-                 |

| Pre-pregnancy weight loss and pregnancy outcome |                                                 |                                   |                                                                                                                                                   |
|-------------------------------------------------|-------------------------------------------------|-----------------------------------|---------------------------------------------------------------------------------------------------------------------------------------------------|
| article                                         | subjects                                        | intervention                      | outcome                                                                                                                                           |
| Glazer
2004(12)                              | 702 with
weight
200-249
lbs            | Weight loss                       | Weight loss of > 10 lbs RR 0,5( 95% CI 0.28-0.92) of
developing gestational diabetes in subsequent pregnancy                                   |
| Dixon
2005
(13)                           | 79 –pre-
operative
weight
125kg
±20 | Laparoscopic
gastric
bypass | After an average weight loss of 28kg - significant decrease in
gestational diabetes, PIH and pre-eclampsia compared to
matched obese cohort |

## **Amendments made to the study protocol**

Protocol version 2 was approved by the Medical Ethics Committee (MEC) of the University Medical Center Groningen at 26-2-2009. The first patient was included and randomized at 9-6-2009. Participating clinics were University Medical Center Groningen, Academic Medical Center, VU Medical Center, Leids University Medical Center, Erasmus Medical Center, Maastricht University Medical Center, University Medical Center Utrecht, Radboud University Medical Center Nijmegen, Deventer Hospital, Rijnstate Hospital, Maximal Medical Center, Onze Lieve Vrouwe Gasthuis, Medical Spectrum Twente, Atrium Medical Center, Isala Clinics, Medical Center Alkmaar, Martini Hospital, Meander Medical Center and Leveste Hospital.

In protocol version 3 the following changes in the study protocol were made (after including 86 patients). The MEC approved version 3 of the protocol at 2-6-2010.

1. Kaplan-Meier survival analyses instead of Chi analyses will be used for statistical analyses. Log-rank tests or Cox analysis can reveal differences in the two study arms.
2. Number of oocytes, embryos and cryo preserved embryos after IVF-ICSI treatment were added as study endpoints.
3. Apgar score, arterial pH and congenital anomalies were added as study endpoints.
4. The upper limit of age was changed from 38 years to 39 years.
5. Women with moderate hypertension (systolic tension 140-159 mmHg and diastolic tension 90-109 mmHg) became eligible if there hypertension was treated.
6. Couples who use donor semen were not eligible.
7. Baseline measurements will be taken by the nurse who randomizes the patient and not by the nurse who provides the lifestyle intervention.
8. We added a questionnaire of weight gain during pregnancy
9. We advised all care providers in case of pregnancy to request an oral glucose tolerance test.
10. Orbis Medical Center, Laurentius Hospital, st. Antonius Hospital, Medical Center Leeuwarden, ZGT Almelo and Jeroen Bosch Hospital were added as participating hospitals.
11. The Radboud UMCN withdrew from study participation. They did not include any patients.

In protocol version 4 (approved at 21-10-10), after inclusion of 188 patients, the following changes in the study protocol were made:

1. Women with a BMI of 40 kg/m^2 or above became eligible for study participation.
2. Number of instrumental deliveries, implementation chance per embryo transfer during the IVF/ICSI procedure were added as study endpoints.
3. We started with collection of cord blood after delivery.
4. The Erasmus MC withdrew from study participation. They did not include any patients.

In protocol version 5, after inclusion of all 577 patients (follow-up was still ongoing), the following changes were made (approved at 13-11-2013).

1. Kaplan-Meier analysis will be used for the secondary endpoint 'ongoing pregnancies'.
2. Complications of fertility treatment were added as study endpoints.
3. We added education and ethnicity to our possible confounding factors.
4. We asked for permission to use the data of this study also in the study of the follow-up of the children born in our trial.

**Costs and effects of a structured lifestyle program in overweight and obese subfertile couples to prevent unnecessary treatment and improve reproductive outcome**

[figure not shown]

## **2. LIST OF ABBREVIATIONS AND DEFINITION OF TERMS**

|     |                           |
|-----|---------------------------|
| SAP | Statistical Analysis Plan |
| TCC | Trial Coordination Center |

### **3. INTRODUCTION**

The purpose of the Statistical Analysis Plan (SAP) is to provide a comprehensive and detailed description of the rationale, methods and presentation of the data analysis for the LIFEstyle study. In this study, efficacy, cost-effectiveness and safety of fertility treatment with and without a lifestyle intervention will be assessed in subfertile obese women.

## 4. PROTOCOL SUMMARY

### 4.1 Study background and rationale

Subfertility affects approximately one in ten couples planning conception. Among subfertile women, about 30% are overweight or even obese. Epidemiological data suggest that the reduction of overweight will increase the chances of conception, decrease pregnancy complications and improve perinatal outcome. In small intervention studies beneficial reproductive effects of improvement of lifestyle leading to a reduction in body weight have been demonstrated. The British Fertility Society advises that fertility treatment be withheld if the body mass index (BMI) is over 35.

In the Netherlands, there is at present no agreed standard of care for subfertile women with overweight or obesity. Some centers simply withhold treatment of couples in whom the woman is overweight or obese, but most fertility centers treat overweight or obese women irrespective of their BMI. In a few centers, support is offered to women to help them lose weight.

In view of this lack of evidence and strong practice variation we propose a randomized clinical trial in overweight and obese subfertile women, in which we compare the costs and effects of a six months structured lifestyle program, aimed at weight loss, to “usual care”. The intervention aims to prevent unnecessary fertility treatment and prevent complications associated with fertility treatment and obesity-related pregnancy complications, thus improving pregnancy chances and perinatal outcome.

### 4.2 Study design

The study is a multicenter randomized clinical trial. Subfertile women (age 18-39) with a BMI of 29 kg/m^2 or above will be included. Exclusion criteria are: azoospermia or donor semen, severe endometriosis, chronic anovulation due to WHO III and endocrinopathies. Women with an untreated pre-existent hypertension or diabetes type 1, or pregnancy-induced hypertension, preeclampsia, eclampsia or HELLP syndrome in a previous pregnancy are excluded.

The intervention consists of a structured lifestyle program of six months, which aims at realistic weight loss of at least 5% to 10%, achieved by the combination of a healthy diet (caloric reduction of 600kCal/day), increase of physical activity (aiming at 10.000 steps per day) and two to three times a week sporting activity, and behavioral modification. The structured lifestyle program, in which practice variation is minimized using a structured software program, has been developed, used and evaluated previously (Zon-MW project 50-

50110-98-078; the Groninger Overweight And Lifestyle study (GOAL)). After six months of lifestyle intervention patients will start fertility treatment as indicated.

In the “usual care” arm fertility treatment will be started if this is justified by the individual prognosis (guideline NVOG)

All randomized women will fill in questionnaires concerning: diet, eating behavior, physical activity and smoking: SF-36, FFQ, DEBQ, Squash list, at inclusion, and at 12 weeks, 6 months, 12 months and 24 months after randomization. Blood samples (10 cc) will be taken at the start, 3 months and 6 months after the start of the study.

#### 4.3 Study flow chart

[figure not shown]

## 5. STUDY OBJECTIVES

The objective of the study is to compare the costs and effects of a six months structured lifestyle program, aimed at weight loss, to “usual care” with the aim to prevent obesity-related pregnancy complications, unnecessary fertility treatment and complications associated with fertility treatment, enhance pregnancy chances and improve perinatal outcome. The control group of women will receive fertility treatment “care as usual” without lifestyle intervention.

### 5.1 Endpoints

#### 5.1.1 General considerations

We aim to estimate the costs and effects of a structured lifestyle program in terms of costs per additional healthy singleton birth rate beyond 37 weeks gestation born after vaginal delivery in a follow-up period of 24 months.

#### 5.1.2 Primary efficacy endpoint

The primary endpoint will be a healthy singleton of more than 37 week gestation born after vaginal delivery. The initial analysis will be done by intention-to-treat, so we will not make a difference for treatment-independent pregnancies and pregnancies that occurred after treatment. Patients who drop out of the study will be analyzed according to their group of randomization. In a per-protocol analysis drop-outs from the lifestyle intervention will be analyzed as non-compliant. For the conventional treatment no difference will be made between the per-protocol and the intention-to-treat analysis.

#### 5.1.3 Secondary efficacy endpoints

Secondary outcome parameters are:

1. Pregnancy outcome and -complications: miscarriage, gestational diabetes, Pregnancy induced hypertension, preeclampsia, HELLP, prematurity < 37 weeks, macrosomia (> p90 (Large for Gestational Age), induction of labour, prolonged duration of labour, operative delivery, assisted delivery and increased blood loss, and multiple pregnancies
2. Percentage of women needing fertility treatment in both groups (OI, IUI, IVF, ICSI) and ongoing pregnancy rates in these treatments.

3. Quality and number of oocytes and embryos and cryo embryos resulting from an IVF or ICSI procedure and the amount of embryos per transfer and implantation rate of transferred embryos
4. Complications during fertility treatment: ovarian hyperstimulation syndrome, infection, tubal pregnancies, torsion (etc).
5. Perinatal outcome: stillbirth, pregnancy duration, body weight, Apgar scores, arterial pH, congenital anomalies and neonatal admission to a neonatal medium, high or intensive care unit.
6. Quality of life, pre-pregnancy body weight, weight gain during pregnancy, waist circumference, behaviour influencing weight, i.e. nutritional habits and exercise pattern, blood pressure, glucose/insulin ratio (HOMA), hormonal profile (androgens, adipokines and cytokines) and costs.

## 6. STATISTICAL METHODS AND REPORTING

### 6.1 Sample size

On the basis of the literature the cumulative live birth rate in a follow-up of two years of subfertility treatment will be 45% for the “usual care” group. The lifestyle intervention group is estimated to have a live birth rate of 60%. We expect an improvement of healthy singleton of more than 37 week gestation born after vaginal delivery from 45% to 60% in the intervention group. Drop-out is expected to be 20% in the intervention arm^4 and is included in the analysis of effectiveness. To prove that, we need to include two groups of 272 women to be included (alpha 0.05, power 80%). To account for 5% lost to follow up 285 women will be included per group. In total, 570 women will be included.

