**Main study parameters/endpoints:**

Primary endpoint is the birth of a healthy singleton after vaginal delivery of at least 37 weeks gestation.

Secondary outcome parameters are number of fertility treatments (OI, IUI, IVF, ICSI), quality and amount of oocytes and embryos and cryo embryos derived in an IVF or ICSI procedure, the amount of embryos per transfer, implantation rate of transferred embryos, complications of fertility treatment, clinical and ongoing pregnancy rates, perinatal outcome, complications and quality of life as well as body weight, waist circumference, behaviour influencing weight, i.e. nutritional habits and exercise pattern, smoking habits, blood pressure, glucose/insulin ratio (HOMA), hormonal profile and costs.

**DATA ANALYSIS:** Analysis will be by intention to treat. Randomisation will be stratified for the presence or absence of anovulation and per treatment center. We expect an

improvement in vaginal singleton delivery beyond 37 weeks from 45% to 60%. Anticipating drop out of 20% in the intervention arm and a 5% loss to follow up in the study, we need to include two groups of 285 women (two-sided test, alpha error .05, beta-error .20).

**STUDY DURATION:** Preparation of the study, including the training of the nurses, will take three months. Inclusion of the couples will take 24 months and the lifestyle intervention will take six months. Follow up is continued for 24 months after randomisation. Database cleaning and analysis of the study will take 6 months. Duration of the study: 57 months

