#### **4.4 Sample size calculation**

**SAMPLE SIZE:** On the basis of the literature the cumulative live birth rate in a follow up of two years of subfertility treatment will be 45% for the “usual care” group (Dutch OFO-study, unpublished data). The lifestyle intervention group is estimated to have a live birth rate of 60% (Dutch OFO-study, unpublished data)

We expect an improvement of healthy singleton of more than 37 week gestation born after vaginal delivery from 45% to 60% in the intervention group. Drop out is expected to be 20% in the intervention arm and is included in the analysis of effectiveness.

To prove that, we need to include two groups of 272 women to be included (alpha 0.05, power 80%). To account for 5% lost to follow up 285 women will be included per group. In total 570 women will be included.

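### The same 45% and 60% are used for live birth and for the stricter primary endpoint, so the stated 80% power is not established for that endpoint

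*Supplement*

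**What the plan says.** SAP 6.1 (Sample size) first states, for usual care, that "the cumulative live birth rate in a follow-up of two years of subfertility treatment will be 45"%. Its lifestyle-arm counterpart reads, in the same words in SAP 6.1 and protocol 4.4, "The lifestyle intervention group is estimated to have a live birth rate of 60"%. The next sentence in both documents moves to the primary endpoint with the same pair: "We expect an improvement of healthy singleton of more than 37 week gestation born after vaginal delivery from 45% to 60"%. No conversion from one outcome to the other is shown.

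The protocol attributes both live birth rates to unpublished cohort data. The SAP attributes the live birth rate to the literature and attaches references 1 to 3 to the endpoint sentence. The protocol summary, under Data analysis, gives only the endpoint version: "improvement in vaginal singleton delivery beyond 37 weeks from 45% to 60"%, with "two-sided test, alpha error .05, beta-error .20". On adherence, SAP 6.1 says "Drop-out is expected to be 20% in the intervention arm" and that this is built into the calculation. The result is 272 women per arm, raised to 285 for 5% loss to follow-up, 570 in total.

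SAP 6.6 lists the two outcomes separately. Live birth is counted whatever the term or health of the child, with a multiple birth counting once. The primary outcome needs a vaginal delivery of a healthy singleton beyond 37 weeks, and twins or higher-order births count as failures.

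**The concern.** A woman who meets the primary endpoint has had a live birth, but the reverse is not true. The two rates can be equal only if no live birth is by caesarean, preterm, multiple or unhealthy. The plan expects such births: prematurity, operative delivery and multiple pregnancy are secondary endpoints (SAP 5.1.3), and the protocol summary gives an odds ratio of 1.3 to 2.4 for caesarean section in overweight or obese women compared with women of normal weight.

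This is the only power statement for the primary endpoint. If the trial shows no significant difference, readers will judge that result against 80% power to detect 45% versus 60%. If the pair describes live birth, that yardstick belongs to another outcome. The economic evaluation, expressed as cost per additional birth of this kind, also depends on the primary-endpoint rates.

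**Working it through.** **Inputs from the documents.** Two-sided alpha 0.05, power 80%, equal arms, rates 45% and 60%, 20% drop-out in the intervention arm, 5% loss to follow-up.

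**Step 1: reproduce the 272.** Assume drop-outs from the programme have the usual-care rate. The lifestyle rate becomes 0.8 × 60% + 0.2 × 45% = 57%. The pooled two-proportion formula is

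n = [1.96 √(2p̄(1−p̄)) + 0.8416 √(p₁(1−p₁) + p₂(1−p₂))]² / (p₂−p₁)².

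With p₁ = 0.45, p₂ = 0.57 and p̄ = 0.51:

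n = [1.96 × 0.7070 + 0.8416 × 0.7019]² / 0.12² = 3.906 / 0.0144 = 271.2, so 272 per arm (power 80.1%).

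This matches the plan exactly. Undiluted, 45% versus 60% would need only 173 per arm. For loss to follow-up, 272 × 1.05 = 285.6, consistent with the stated 285.

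**Step 2: separate the outcomes.** Let f be the share of live births that meet the primary endpoint. The documents do not give f, so it is an assumption. The values below run from 90% down to 57%; the low end corresponds to assumed rates of 30% caesarean, 10% preterm and 10% multiples, multiplied as if independent (0.70 × 0.90 × 0.90 = 0.567). With f equal in both arms, the usual-care rate is 0.45f and the diluted lifestyle rate is 0.57f. Power at n = 272 per arm is

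Φ{ [d − 1.96 √(2p̄(1−p̄)/n)] / √[(p₁(1−p₁) + p₂(1−p₂))/n] }.

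For f = 65%: p₁ = 0.2925, p₂ = 0.3705, d = 0.078. Then (0.078 − 1.96 × 0.04037) / 0.04023 = −0.028, and power is 49%.

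**Step 3: what would keep 80%.** For each usual-care rate I solved for the difference that 272 per arm detects with 80% power. I then solved for the qualifying share q that programme completers would need, with live birth still rising to 60%: diluted lifestyle rate = 0.8 × 0.60q + 0.2 × 0.45f.

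| f | Usual care vs diluted lifestyle | Power at 272 | n per arm for 80% | Detectable difference (points) | q needed in completers |
|---|---|---|---|---|---|
| 100% | 45.0% vs 57.0% | 80% | 272 | 12.0 | 100% |
| 90% | 40.5% vs 51.3% | 72% | 334 | 12.0 | 92% |
| 80% | 36.0% vs 45.6% | 63% | 411 | 11.8 | 85% |
| 65% | 29.3% vs 37.1% | 49% | 571 | 11.4 | 73% |
| 57% | 25.7% vs 32.5% | 42% | 691 | 11.1 | 66% |

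The fourth column shows scale only; it is not a proposal to enrol more.

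**Step 4: the reverse reading.** If 45% and 60% are true endpoint rates, live birth must be 0.45/f and 0.60/f. At f = 90% that is 50% and 67%; at f = 65%, 69% and 92%. Under any f below 100%, the live birth rates printed in the same paragraph are too low.

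**The case against.** Three points on the other side have force.

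First, the arithmetic is correct for the rates entered. A reader might infer that the sample size was miscalculated, but Step 1 shows it was not.

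Second, a reader might infer that 45% and 60% are certainly live birth rates carried over to the endpoint. The documents do not settle that. Protocol 6.1.1 and SAP 6.4 both use live birth as shorthand for the primary outcome, the protocol summary gives the pair for vaginal term singleton delivery alone, and the SAP's references 1 to 3 follow the endpoint sentence. The pair may be endpoint rates with live birth loosely labelled, or the reverse. The sources cannot be seen here. What stands is that the two statements conflict, whichever label is wrong.

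Third, a reader might infer that the design does not have 80% power. That goes too far. The loss in Step 2 requires the same f in both arms, while the protocol's secondary objectives ask whether the programme reduces premature birth, operative delivery and multiple pregnancy, which are the events that disqualify a live birth. If the full 12-point diluted difference held at a lower usual-care rate, power would be 80.3% at 40%, 81.4% at 35% and 83.2% at 30%. For f from 77.5% down to 56.7%, a rise of about 5 to 9 points in completers keeps 80%. However, that rise must come on top of the full gain in live birth, and the plan neither argues nor quantifies it.

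The base rates behind the low end of f are also outside assumptions. If multiples are often preterm or delivered by caesarean, the events overlap, f is higher and the loss is smaller.

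**Conclusion.** The inconsistency is certain: one pair of rates is assigned to an outcome and to a strict subset of it, with no conversion. The 80% power is therefore not established for the primary endpoint, and it is probably lower. As an illustration resting on an assumed qualifying share of 90% to 57%, equal in both arms, and on the plan's 20% dilution, power at 272 evaluable per arm is about 72% to 42%. These are not estimates of the trial's actual power, because the documents give no qualifying share and the programme might raise it.

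No endpoint, analysis set or test is affected, and the planned relative risks with 95% confidence intervals allow a null result to be judged on its interval. What needs correcting is the power statement that readers will set beside that result.

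**What to change.** In SAP 6.1, protocol 4.4 and the protocol summary, state which outcome 45% and 60% describe.

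If it is live birth, say that 272 evaluable women per arm (285 enrolled, 5% loss) give 80% power for live birth of 45% versus 57% after 20% dilution. Then give, for the primary endpoint:

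- a justified usual-care rate, or a range if no source exists (the cohort data may not record mode of delivery, term and plurality);
- the resulting power at 272 evaluable per arm, saying whether the qualifying share is taken as equal in both arms or expected to rise, and why;
- the difference detectable with 80% power, about 11 to 12 points for usual-care rates of 26% to 41%.

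If the pair describes the primary endpoint, correct the live birth rates upward and cite their source.

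Keep the planning assumption on record with an annotation. Do not go on presenting 45% to 60% as the expected primary-endpoint rates unless the live birth rates are corrected.

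The cost is a change of wording in two documents and a power statement that may look less favourable. No further enrolment is asked for; the amendment log shows that all 577 women had been included before protocol version 5.
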